### Experimental condition

The program consists of six group-based meetings with 8 to 10 participants and individual homework assignments. “Doelbewust!” is a protocol-based psychosocial educational program. *Doelbewust* is the Dutch word for “purposefully” and we have translated this program name into English as “Right On Target”. The program is led by a trained nurse. Participants are introduced to different goal management strategies and learn to use these strategies to cope in a flexible way with threatened personal goals. The goal management strategies that are covered in the program are: goal maintenance, goal adjustment, goal disengagement, and goal reengagement [39-42].

Table 2 lists the topics, goals, and applied techniques for each meeting of the program. The general structure of each meeting is as follows: a short review of the contents of the previous meeting; introducing the topics of the current meeting; elaborating the topics by group discussions and by practicing in individual, dual and group exercises; and explaining homework assignments for the next meeting. A pilot was executed to test the feasibility of the program protocol.

**Table 2 T2:** Contents of the goal management program

**Meeting**	**Topic**	**Main goals meeting**	**Applied techniques**^**#**^
1.	Arthritis in daily life	Become aware of the influence of polyarthritis in the different domains of life.	Information (general), instruction, problem identification, behavioral information (narratives), modeling (by narratives), vicarious reinforcement (narratives), comparison (with narratives and other participants), emotional social support (by other participants), set homework tasks, prompt (email after meeting to do homework).

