#### Direct medical costs

Medical costs are collected on a bimonthly basis. Patients are asked the number of telephone consultations they have with their GP, as well as their number of visits to the GP, medical specialist, other paramedical and alternative therapists, and hospital days.

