#### Indirect non-medical costs

Indirect non-medical costs are collected at the same frequency as the direct medical costs. Patients are asked about their absenteeism from work, domestic care, domestic help, and informal care.

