#### Price estimate

Participants in the program group are asked at the post-intervention T1 measurement how many euros they would spend for participation in this program if no health insurance would pay the costs.

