### Measures for the competence of group trainers

During the first two courses, the trainers receive one-hour supervision after every session, and afterwards supervision occurs less frequently, but on a regular basis. Random sessions are recorded with a voice recorder and checked for correct delivery of the protocol.

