#### Economic evaluation

Results will be expressed as quality-adjusted life years (QALYs). The time-integrated summary score, which is the area under the curve (AUC) of the utilities, will be calculated to define the quality of life per time period (0–2 months and 0–8 months). Between-group differences in QALYs will be analyzed per period using t-test for unpaired observations. The costs will be presented as an arithmetic mean (+− SD) per patient per group. The between-group differences in resource use will be analyzed per period using the Mann–Whitney U test. For every patient and study period, the mean incremental costs will be calculated, and, using double-sided bootstrapping, 95% confidence intervals (95%CI) will be estimated. The incremental cost utility ratio (ICER) will be calculated by dividing the extra costs for the goal management intervention by the extra QALYs derived from the goal management intervention. The ICER will be expressed as costs per QALY gained. The 95% confidence intervals of the ratios will be estimated with bootstrapping. Cost evaluations will be conducted from the societal perspective and with a time-horizon of less than one year. Due to this short time-horizon, costs and effects will not be discounted.

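### The economic evaluation is labelled societal, but the cost items it names leave out participants' travel and non-work time for the six meetings

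*Protocol article*

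**What the plan says.** The Economic evaluation section sets the perspective and horizon: "Cost evaluations will be conducted from the societal perspective and with a time-horizon of less than one year". It obtains the ICER by "dividing the extra costs for the goal management intervention by the extra QALYs derived from the goal management intervention" and does not itemise that numerator.

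The inputs are named under Measures for the economic evaluation:

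- Direct medical costs: "Patients are asked the number of telephone consultations they have with their GP"; contacts in person with doctors and therapists, and days spent in hospital, are counted too.
- Indirect non-medical costs: "Patients are asked about their absenteeism from work, domestic care, domestic help, and informal care".
- Price estimate: at T1, program participants are asked "how many euros they would spend for participation in this program if no health insurance would pay the costs".

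Table 3 gives three open-ended items for direct medical costs and seven for indirect non-medical costs, each at T0 to T4. It has no row for direct non-medical costs.

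On exposure, the Experimental condition section says: "The program consists of six group-based meetings with 8 to 10 participants and individual homework assignments". Under Control condition, the waiting list is offered the program only at eight months, directly after the last follow-up.

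**The concern.** A societal perspective is normally taken to count costs whoever bears them, including those borne by participants. Attending six meetings costs each participant travel and time, and the named items have no place for either. The willingness-to-pay question does not fill the gap: it records a hypothetical price and is put to the program group only.

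The gap is one-sided. Controls do not attend the program inside the costing window, so the missing cost does not cancel between the arms. Resampling does not help either, because a bootstrap of recorded costs cannot restore a cost that was never recorded. The error would favour the prediction in the Discussion that the program will be cost effective. The QALY difference over eight months is likely to be small, so even a modest missing cost can move the ratio noticeably.

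**Working it through.** The document states no cost, unit price, QALY gain or ICER, so there is no figure of the plan's own to reproduce on this point. The check has two parts: match the items to the label, then show direction and scale.

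**1. Items against the label**

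| Cost caused by attending | Named item that would record it |
|---|---|
| Paid work hours missed | Absenteeism (possibly) |
| Non-work time at meetings and in travel | None |
| Travel expense | None |

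**2. Timing and arm.** T4 is six months after the program ends and also marks eight months after entry, so the program occupies about 8 − 6 = 2 months. The whole cost of attending therefore falls in the 0–2 month period and is contained in the 0–8 month period. It falls in the program arm only.

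**3. Direction.** Let C be the recorded incremental cost, c > 0 the omitted cost per program participant, and q the QALY gain.

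- Full ICER = (C + c)/q; ICER as recorded = C/q.
- Difference = c/q, which is positive when q > 0.
- The incremental cost itself is understated by c whatever the sign of q.

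**4. Scale, with assumed values only.** c = 6 × (session hours + return travel hours) × hourly value + 6 × travel expense per meeting.

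| Assumption set | Session h | Travel h | Euros/h | Travel expense per meeting | Time cost | Travel expense, total | c |
|---|---|---|---|---|---|---|---|
| Low | 1.5 | 0.5 | 8 | 3 | 6 × 2 × 8 = 96 | 18 | 114 |
| Middle | 2 | 1 | 12 | 6 | 6 × 3 × 12 = 216 | 36 | 252 |
| High | 3 | 1.5 | 20 | 12 | 6 × 4.5 × 20 = 540 | 72 | 612 |

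A gain of 0.01 to 0.03 QALY over 8/12 year is a mean utility difference of 0.01/(8/12) = 0.015 to 0.03/(8/12) = 0.045.

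| c (euros) | c/0.03 | c/0.01 |
|---|---|---|
| 114 | 3,800 | 11,400 |
| 252 | 8,400 | 25,200 |
| 612 | 20,400 | 61,200 |

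**5. Allowing for absenteeism.** In the extreme case where the absenteeism question already captured every hour of session and travel time, only travel expense would be missing. The shift would then run from 18/0.03 = 600 to 72/0.01 = 7,200 euros per QALY. The truth depends on how many participants are employed and miss work to attend. Homework time is in none of these figures.

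**The case against.** The strongest reply is that this is a journal article, which condenses costing detail, and that silence is not exclusion. Table 3 counts seven indirect items while the text names four categories, and the item wording is not shown. Some travel or time question could exist. Absenteeism may already catch paid hours. How leisure time is valued under a societal perspective is a costing choice. The analysis is not primary, and the section on strengths and limitations of the trial makes it conditional on an effect being found.

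Much of this stands. It makes the bias conditional, rules out any firm magnitude, and means that absenteeism must be netted out. It does not remove the mismatch. The article does not simply leave costing to another document: it names its cost categories and its perspective, and the categories do not cover what the perspective implies. The extra items in Table 3 may be no more than sub-questions of the four named categories. The condition on an effect points the other way, since the ICER is then reported mainly where a benefit is seen, the setting in which the omission flatters the program.

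A reader might go further and infer that delivery is left out too: nurse hours, the full-day trainer course and psychologist supervision, of which the article says "During the first two courses, the trainers receive one-hour supervision after every session". The documents do not support that. The two cost lists describe what patients are asked, and patients would not be asked for staff hours. Such hours would come from program records, and the numerator is worded broadly enough to include them.

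**Conclusion.** The point holds in limited form. The stated societal perspective is wider than the named cost items, which omit participants' travel and non-work time for the meetings. If these costs are left out and the QALY gain is positive, the ICER is understated by c/q in the program's favour. The direction follows from the design. The size does not, because hours, prices, travel and QALY gains are all assumptions; the illustration gives several thousand to tens of thousands of euros per QALY for time and travel together, and less where absenteeism already catches the time.

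It should not be concluded that the ICER is too favourable as a settled fact, or that program delivery goes uncosted. The first depends on actual omission and on q > 0, and the second is not shown. The efficacy analyses are untouched.

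**What to change.** Take one of two routes.

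1. Keep the societal label. Under the economic measures and in the Economic evaluation section, add for the program arm: meetings attended × (session length + return travel time) × a stated unit price, plus travel cost by distance to the site. Exclude hours already reported as absenteeism, to avoid double counting. Count the result in the 0–2 month period and carry it into 0–8 months.
2. Otherwise, replace the societal label with the narrower perspective that the listed items support.

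As a clarification only, one sentence could confirm that delivery, trainer training and supervision enter the numerator.

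The cost is small. Trainers already complete a form after each session, on which attendance can be noted, and distance can be taken from postcodes. No extra visits are needed. The downside of the first route is a little more costing work and a slightly less favourable ICER; that of the second is a narrower claim.

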## Discussion

The purpose of the presented study protocol is to evaluate the effectiveness of the “Right On Target” program, a newly developed goal management intervention. We predict that the experimental condition will show positive effects compared with usual care in reducing depressive and anxiety symptoms and in improving positive affect, purpose in life and social participation, and will be cost effective. Both the program itself and its evaluation are likely to add to the existing body of knowledge in several ways, as described below.

### Strengths and limitations of the goal management intervention

To the best of our knowledge “Right On Target” is the first program that focuses on the four goal management strategies of goal maintenance, goal adjustment, goal disengagement and goal reengagement to support improvement of adaptation to a chronic disease. The possibility to tailor the program to the personal needs of participants is expected to increase its effectiveness and participants’ commitment to the program.

We provided a detailed description of the ingredients of the intervention, in accordance with the argument of Michie et al. [61], in order to communicate applied techniques that support the development of effective interventions and to improve knowledge regarding effective behavior change techniques. We hope to be able to identify the active ingredients in our intervention by clearly stating the underlying theory and assumed mechanisms of behavioral change.

Furthermore, the present study incorporates a holistic focus on adaptation, as the outcomes assessed are both the absence of psychological distress and the presence of well-being. Hence, this research focuses not only on the difficulties that people may experience due to a chronic disease, but also on personal sources of resilience.

As stated earlier in this paper, the goal management program focuses on dealing with threatened personal goals, rather than a pre-defined focus on disease-related goals. This program may ask for different competencies than health professionals are used to deploying in their daily practice. The specialized nurses in rheumatology care who provide the program have undergone extensive training. During the study period, the nurses receive regular guidance and supervision. Nevertheless, it is possible that nurses find it difficult to “sit on their hands” and not provide immediate solutions. This program might be less suitable without the extensive training and guidance of the nurses.

### Strengths and limitations of the randomized controlled trial

Our study will hopefully answer questions regarding the effectiveness of the goal management intervention for patients with a rheumatic disease. We try to understand the pathways that are responsible for successful adaptation in persons dealing with a rheumatic disease and investigate who benefits most. In addition, we have included an economic evaluation. However, these additional analyzes cannot be conducted in absence of an effect of the goal management intervention compared to the waiting list group.

As the “Right On Target” program is a newly developed intervention, we execute a stakeholders’ analysis. Experiences of participants, trainers and the management of the participating clinics provides insight into the feasibility regarding the intervention. The information from the stakeholders’ analysis supports future implementation of the intervention.

## Conclusion

To test the effectiveness of the “Right On Target” program to increase adaptation to polyarthritis, a randomized controlled trial is needed and a design for this study is presented. Results from this trial will test the effectiveness of the “Right On Target” program in improving the adaptation of patients to polyarthritis in terms of the absence of psychological distress and the presence of well-being. The protocol for the randomized controlled trial reflects a comprehensive view both on adaptation and on goal management. The presented study will add to the existing body of knowledge of health promotion interventions.
